#### 8.5 Other treatments

In both the intensive therapy and conventional therapy arms, all subjects with a history of cardiovascular disease are to be given anti-platelet and anti-coagulant therapy such as low-dose aspirin (enteric tablets) in accordance with the Guidelines. All subjects who are already receiving such therapy are to be given the same treatment in both the intensive therapy and conventional therapy arms.

The physician in charge may at his/her discretion use any drugs other than those defined in 8.2, 8.3 and 8.4 for glycemic, blood pressure and lipid control.

#### 8.6 Random assignment

The study subjects are to be assigned to the investigational treatment in which the responsibility for such assignment is to rest solely with the trial statistician, and the allocation code used is not to be disclosed to any of the healthcare institutions or physicians participating in the study. In random assignment, dynamic allocation is used with the presence or absence of cardiovascular disease (myocardial infarction, stroke, coronary bypass surgery, percutaneous coronary angioplasty, cerebral revascularization\*1, or cerebrovascular reconstruction\*2), male/female ratio, age ( $\geq 60$ , < 60 years old) and HbA1c ( $\geq 8.9\%$ , < 8.9%) serving as adjustment factors to ensure a balanced allocation of the subjects between the treatment arms, and the trial statistician is to record the algorithm used in allocation in a separate document.

Note: Cerebral revascularization\*1: Carotid endarterectomy, percutaneous angioplasty, and stent placement  
Cerebrovascular reconstruction\*2: Thrombolysis

## 9. Observation/evaluation schedule

An outline of the observation/evaluation schedule for the study is shown in Table 2.

Table 2. Observation/evaluation schedule: an outline\*1

|                                                                                                                                         | At informed consent *2 | At final study registration | At regular hospital visits *3 | Every 6 months | Every 12 months |
|-----------------------------------------------------------------------------------------------------------------------------------------|-----------------------------------|-----------------------------|------------------------------------------|----------------|-----------------|
| Height                                                                                                                                  |                                   | ○                           |                                          |                | ○               |
| Waist circumference                                                                                                                     |                                   | ○                           |                                          |                | ○               |
| Body weight                                                                                                                             |                                   | ○                           | ○                                        | ○              | ○               |
| Blood pressure control                                                                                                                  | ○                                 | ○                           | ○                                        | ○              | ○               |
| Glucose level, HbA1c *4                                                                                                      | ○                                 | ○                           | ○                                        | ○              | ○               |
| Total cholesterol, LDL-C *5 (non-HDL-C *6 ), HDL-C, TG                                                            | ○                                 | ○                           | ○                                        | ○              | ○               |
| Hematologic examinations *7 , hepatic/renal function test *8 , CPK, serum electrolytes (Na, K *9 , Cl) | ○                                 | ○                           | ○                                        | ○              | ○               |
| Urinary albumin *10 , urinary creatinine (to be measured in the same sample)                                                 |                                   | ○                           | (○) *11                       | ○              | ○               |
| Brain natriuretic peptide (BNP)                                                                                                         | (○) *12                |                             |                                          |                |                 |
| Chest x ray, ECG, fundus examination                                                                                                    | ○                                 |                             |                                          |                | ○               |
| Parameters to be examined centrally *13                                                                                      |                                   | ○                           |                                          |                | ○               |

\*1 Hematologic examinations scheduled at the time of informed consent (from the time of consent obtained until before interim study registration), at official study entry and every 12 months are to be performed in fasting states.

\*2 Examinations scheduled at the time of informed consent are to be performed from the date consent obtained until before interim study registration.

Items to be examined during this time include: blood pressure control, total cholesterol, LDL-cholesterol (non-HDL-cholesterol), HDL-cholesterol, triglycerides

Chest x ray, echocardiogram (ECG), fundus examination (by an ophthalmologist)

(Available data on these examinations that is up to 6 months old may alternatively be used)

Hepatic/renal function test (serum creatinine), BNP (only in those suspected of meeting the relevant exclusion criteria)

\*3 These are to be examined on a regular basis during the entire study period in conjunction with the hospital visits planned for each subject.

\*4 Only stable HbA1c is to be measured and adjusted against reference material.

\*5 To be estimated by using the Friedewald formula ( $\text{LDL-C} = \text{total cholesterol} - \text{HDL-C} - \text{TG} \times 1/5$ ), except in those with TG levels  $\geq 400$  mg/dL.

\*6 To be estimated by using the formula:  $\text{non-HDL-C} = \text{total cholesterol} - \text{HDL-C}$

\*7 This includes white blood cell count, red blood cell count, hemoglobin, hematocrit, and platelet count.

\*8 This includes AST, ALT,  $\gamma$ -GPT, LDH, BUN, and serum creatinine.

\*9 Those in whom the potassium level ranged between 5.6 and 5.9 mEq/L are to be re-examined. Those in whom the potassium level exceeded 6.0 mEq/L are to be re-examined and treated appropriately.

\*10 Urinary albumin is to be evaluated for amount of its excretion per 1 g of urinary creatinine, and to be evaluated in morning urine samples at final study registration and every 12 months.

\*11 Those who had an episode of nephropathy are to be re-examined within 3 months of its occurrence using a morning urine sample.

\*12 To be performed only in those suspected of meeting the relevant exclusion criteria (including myocardial infarction, angina or a history of angina, a history of coronary bypass surgery, a history of percutaneous coronary angioplasty, other cardiac disease, ECG findings of left ventricular hyperplasia, and abnormal ECG findings)

\*13 Items to be examined and the timeline for these examinations are described in section 9.6.

### Examination dates

- Examinations scheduled for implementation at patient hospital visits every 6 months and every 12 months (except

chest X-ray, ECG and fundus exams) are to be performed between 1 month before the predetermined date and 1 month after that date.

- Available chest x ray, ECG and fundus exams that are up to 6 months old may alternatively be used. These examinations scheduled every 12 months are to be performed between 2 months before the predetermined date and 2 months after that date.
- Final study registration is to be completed one day after but within 3 months of the date of informed consent.

### **9.1 Items to be examined at informed consent (from the time of informed consent until before interim study registration)**

The physician in charge is to perform the following examinations after informed consent was obtained from the subjects but before their final study registration. Hematologic examinations are to be performed in fasting states.

Blood pressure control

HbA1c, total cholesterol, LDL-cholesterol (non-HDL-cholesterol), HDL-cholesterol, triglycerides

Chest x ray, echocardiogram (ECG), fundus examination

(Data from these exams that are 6 months old or more recent may alternatively be used).

Hepatic/renal function test (serum creatinine), BNP (only in those suspected of meeting the relevant exclusion criteria)

### **9.2 Items to be examined at final study registration**

The physician in charge is to perform the following examinations at the subjects' final study registration. Hematologic examinations are to be performed in fasting states.

Height, body weight, blood pressure, waist circumference

Fasting plasma glucose, HbA1c, total cholesterol, LDL-cholesterol (non-HDL-cholesterol), HDL-cholesterol, and triglycerides

Hematologic examination (white blood cell count, red blood cell count, hemoglobin, hematocrit, and platelet count), hepatic/renal function test (AST, ALT,  $\gamma$ -GTP, LDH, BUN, and serum creatinine), serum electrolytes (Na, K, and Cl), CPK, urinary albumin (to be measured in a morning urine sample), urinary creatinine (to be measured in the same sample used for urinary albumin measurement), family history, maximum body weight in the past, and disease duration

### **9.3 Items to be examined at regular hospital visits**

The subjects are to be evaluated for the following parameters at their regular hospital visits. Hematologic examinations may be performed in non-fasting states.

Body weight, blood pressure control

Blood glucose, HbA1c, total cholesterol, LDL-cholesterol (non-HDL-cholesterol), HDL-cholesterol, and triglycerides

Hematologic examination (white blood cell count, red blood cell count, hemoglobin, hematocrit, and platelet count), hepatic/renal function test (AST, ALT,  $\gamma$ -GTP, LDH, BUN, and serum creatinine), serum electrolytes (Na, K, and Cl), and CPK

### **9.4 Items to be examined every 6 months**

The subjects are to be evaluated for the following parameters every 6 months. Hematologic examinations may be performed in non-fasting states.

Body weight, blood pressure control

Blood glucose, HbA1c, total cholesterol, LDL-cholesterol (non-HDL-cholesterol), HDL-cholesterol, and triglycerides

Hematologic examination (white blood cell count, red blood cell count, hemoglobin, hematocrit, and platelet count), hepatic/renal function test (AST, ALT,  $\gamma$ -GTP, LDH, BUN, and serum creatinine), serum electrolytes (Na, K, and Cl), and CPK

Urinary albumin, urinary creatinine (to be measured in the same sample used for urinary albumin measurement)

### **9.5 Items to be examined every 12 months**

The subjects are to be evaluated for the following parameters every 6 months. Hematologic examinations are to be performed in fasting states.

Height, body weight, blood pressure control, waist circumference

Fasting plasma glucose, HbA1c, total cholesterol, LDL-cholesterol (non-HDL-cholesterol), HDL-cholesterol, and triglycerides

Chest x ray, echocardiogram (ECG), fundus examination

(Data from these exams obtained within 2 months before or after the predetermined examination date may alternatively be used. The fundus examination is also to be performed within 6 months prior to the end of the study.).

Hematologic examination (white blood cell count, red blood cell count, hemoglobin, hematocrit, and platelet count), hepatic/renal function test (AST, ALT,  $\gamma$ -GTP, LDH, BUN, and serum creatinine), serum electrolytes (Na, K, and Cl), CPK, urinary albumin (to be measured in a morning urine sample), urinary creatinine (to be measured in the same sample used for urinary albumin measurement)

**9.6 Clinical parameters to be examined centrally**

High-sensitive C-reactive protein (hs-CRP), insulin, adiponectin, and glycoalbumin (GA) are to be examined centrally, using the same samples as for routine measurements. High-sensitive CRP, insulin and GA are to be evaluated at the time of final study registration and every 12 months while adiponectin will be evaluated at the time of final study registration, in March 2013, and at study completion. Residual samples are to be sent to the designated laboratory (SRL) by the Principal Investigator in accordance with the "Ethical Guidelines for Medical and Health Research Involving Human Subjects" and are to be retained appropriately in accordance with the standard operating procedures (SOP).

**9.7 Other surveys**

Questionnaire-based surveys are to be conducted in subjects prior to final study registration\*1 as well as after 1 and 3 years and at study completion. Subjects who discontinue treatment will be surveyed at the time of discontinuation. In addition, a cognitive function test will be performed at the end of the study. The details of these surveys to be conducted are described in a separate document.

If an assessment of risk factors or frequency of events, other complications, and adverse drug reactions is required, additional parameters will be measured at the central laboratory using residual samples or clinical information will be collected using questionnaires or other tools.

Note:\*1 To be performed after informed consent was obtained from each subject but prior to his/her final study registration.

**9.8 Reporting the Data Center**

If a macrovascular or microvascular complication occurred in a particular subject, its finding/diagnosis, date of its occurrence, and its causal relationship are to be reported to the Data Center.

To facilitate evaluation of the predetermined endpoints, when myocardial infarction or a coronary event occurred in a particular subject, a photocopy of the echocardiogram (ECG) chart used as a basis for the subject's eligibility evaluation as well as of the ECG chart at the time of the event occurrence is to be submitted to the Data Center. These copies are to be submitted in such a way that the subject can in no way be identified by the Data Center.

**9.9 Feedback from the Data Center**

The Data Center is to make inquiries to the participating healthcare institutions as to body weight, HbA1c, blood pressure control, and lipid control profile in the subjects assigned to the intensive therapy arm every 6 months to evaluate if they have achieved the management goals for these parameters, and encourage the institutions to ensure these goals are achieved.

**9.10 General investigations**

During the course of the study, general investigations are to be performed on a regular basis to keep track of the incidence of cardiovascular events as well as to see if the study is in progress exactly as planned.

These general investigations are intended to survey on the occurrence of cardiovascular events during designated time periods. Items to be surveyed include diagnosed events, date of their occurrence, date of examination for event evaluation and event details; or if there were no events to be reported, an indication to that effect as well as the date of final confirmation.

## 10. Efficacy evaluation

### 10.1 Primary endpoint

The primary endpoint of the study is defined as the "occurrence of either of myocardial infarction, coronary bypass surgery, percutaneous transluminal coronary angioplasty, stroke, carotid endarterectomy, percutaneous transluminal cerebral angioplasty, carotid artery stenting, or death (irrespective of its causes)".

### 10.2 Secondary endpoints

The secondary endpoints of the study are defined as the following four events.

1. Occurrence of either of myocardial infarction, stroke, or death
2. Onset or progression of nephropathy
3. Occurrence of lower limb vascular events (amputation or revascularization of lower limb)
4. Onset or progression of retinopathy

### 10.3 Definition of the endpoints used

#### A) Myocardial infarction

Myocardial infarction is defined as the presence of typical symptoms (e.g., lasting severe chest pain), echocardiographic changes, abnormal laboratory findings (e.g., elevation of the cardiac enzyme troponin T), or findings of clinical imaging (e.g., coronary angiography, cardiac scintigraphy, multi-detector row computed tomography) which were diagnosed as such by a physician.

#### B) Stroke

Stroke is defined as the presence of a newly onset focal symptom lasting more than 24 hours which was diagnosed as such by a physician (preferably with the culprit lesion identified/confirmed on CT or MRI/MRA).

#### D) Onset or progression of retinopathy

When either of the following occurs unilaterally or bilaterally, that time point is to be construed as the occurrence of an event.

- a. Progression from absence of retinopathy to non-proliferative retinopathy or proliferative retinopathy
- b. Progression from non-proliferative to proliferative retinopathy
- c. Loss of vision likely due to retinopathy

### 10.4 Assessment of the endpoints

A separate Endpoint Assessment Committee is to be put in place for macrovascular complications, nephropathy, and retinopathy to verify each of the events that constitute the primary and secondary endpoints of the study.

### 10.5 Reporting on events

In the event that a new event related to any of the study endpoints was found to have occurred in a particular subject after his/her final study registration, the physician in charge is to report on that event to the Data Center. The Endpoint Assessment Committees are to be convened every 6 months to review each of the events reported in depth.

Even when an event defined as a primary or secondary endpoint occurred in a particular subject, the subject is to continue to be part of the study and observed for occurrence of other events.

## 11. Safety evaluation

### 11.1 Technical terminology

In the present study, “adverse reactions” and “side effects” are defined as followed.

- Adverse reactions

Adverse reactions are defined as any untoward (or unintended) symptoms and signs (including abnormal laboratory findings) that may or may not be causally related to the investigational treatment. In other words, all untoward symptoms or signs that occurred in the study subjects, including those whose causal relationship to the investigational treatment can be ruled out, are to be recorded as “adverse reactions”.

In this trial, all untoward laboratory findings that occurred after the start of the study are to be handled as adverse reactions, in addition to all symptoms and signs that newly occurred or worsened after the start of the study.

- Side effects

Of the untoward (or unintended) symptoms and signs (including abnormal laboratory findings), those whose causal relationship to the investigational treatment cannot be ruled out are defined as side effects. In other words, of the “adverse reactions” defined above, those whose causal relationship to the investigational treatment cannot be entirely ruled out are to be handled as side effects.

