## 6. Study design

### 6.1 Processes

The present trial is a multi-center, open-label, randomized parallel-group study conducted to compare the efficacy of intensive versus conventional therapy in type 2 diabetic patients with HbA1c 6.9% or greater. The overall procedure from patient informed consent to completion of patient data evaluation is as described below.

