#### Procedure 3:

Identify symptoms not perceived by the subjects by auscultation and percussion. Additionally, identify changes in the laboratory and vital signs data that may be clinically significant or meaningful. The physician in charge may use his/her judgment in deciding which change (e.g., in laboratory findings) may be construed as “clinically meaningful”.

The physician in charge is to handle symptoms and signs that newly occurred or worsened after the start of the study as adverse reactions, of all symptoms, signs and changes in laboratory findings, and to deal with them appropriately, to follow up on these symptoms and signs until they disappear, resolve or return to their baseline status, and to describe the name(s) of the adverse reaction(s), date of their occurrence, their extent, their causal relationship to the investigational treatment, their severity, and how they were dealt with (e.g., the investigational drug was reduced or discontinued or switched to another drug), their outcome, and date their outcome confirmed in a case report form.

In the event that the physician in charge judged follow-up unnecessary before these symptoms and signs disappear, resolve or return to their baseline status, he/she is to give reasons for such decision in the case report form.

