### **12.3.3 Other analyses**

To complement analyses of the primary endpoints, three kinds of analyses (descriptive statistics, hypothesis testing and effect size estimates) are to be performed on the secondary endpoints. However, being exploratory in nature, these analyses are not to be adjusted for multiplicity.

Fisher's direct exact probability estimation is to be used to compare the percentages of occurrence of adverse reactions between the two treatment arms as part of the safety evaluation, and 95% confidence intervals (CI) for the differences detected. Accurate confidence intervals are to be estimated based on the bimodal distribution of the data.

Otherwise, exploratory analyses are to be performed as required. When such analyses are to be performed, their details

are to be described in the Statistical Analysis Plan.

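### Sections 11.1 and 11.2 give unreconciled rules for counting laboratory findings as adverse reactions, so the laboratory part of the between-arm comparison in 12.3.3 is open to differential ascertainment in an open-label trial

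*Protocol*

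**What the plan says.** Protocol section 11.1 defines adverse reactions as "any untoward (or unintended) symptoms and signs (including abnormal laboratory findings) that may or may not be causally related to the investigational treatment". It adds a rule specific to this trial: "all untoward laboratory findings that occurred after the start of the study are to be handled as adverse reactions". No degree of abnormality or clinical significance is required.

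Section 11.2, Procedure 3, describes collection differently. The physician in charge is to "identify changes in the laboratory and vital signs data that may be clinically significant or meaningful". The choice is left to that physician: "The physician in charge may use his/her judgment in deciding which change (e.g., in laboratory findings) may be construed as" clinically meaningful. No threshold is given for any analyte. The next paragraph does not repeat the restriction to meaningful changes; it treats "symptoms and signs that newly occurred or worsened after the start of the study as adverse reactions, of all symptoms, signs and changes in laboratory" results.

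Section 6.1 states the design: "The present trial is a multi-center, open-label, randomized parallel-group study". In section 12.3.3, Fisher's "direct exact probability estimation is to be used to compare the percentages of occurrence of adverse reactions between the two treatment arms", with 95% confidence intervals for the differences. The protocol does not say which of the two laboratory rules supplies the counts.

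**The concern.** A between-arm comparison of percentages means something only if a case is found in the same way in both arms. Here the protocol can be followed in two ways, and neither secures this for laboratory findings.

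If sites follow Procedure 3, a laboratory change becomes an adverse reaction when a physician who knows the allocation thinks it matters. A physician titrating drugs by protocol steps may view a raised value differently from one giving guideline care. If sites follow 11.1 literally, the count depends on how often blood is taken, and the protocol fixes the visit frequency for one arm only.

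This matters because section 11.6 lists laboratory items among the anticipated reactions: high CPK, leucopenia, thrombocytopenia, hyperkalemia and abnormal GOT/GPT. The rationale in section 11.2 itself argues that safety data from many sites cannot be combined without common collection procedures. The active checklist meant to provide this covers four symptoms and no laboratory item.

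**Working it through.** The protocol states no figure on this point, so there is nothing to reproduce. The check is a comparison of the text, followed by arithmetic that shows scale only.

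**1. The rules side by side**

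| Element | Section 11.1 | Section 11.2, Procedure 3 |
|---|---|---|
| Which laboratory findings count | All untoward ones after study start | Changes that may be clinically significant or meaningful |
| Who decides | Not stated | Physician in charge, by own judgement |
| Threshold | None | None |

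No sentence equates *untoward* with *clinically meaningful*, and neither section refers to the other's rule.

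**2. Route through judgement (11.2)**

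Let p be the true proportion with an abnormal laboratory finding, equal in both arms, and q the share judged meaningful. The reported percentage is p × q.

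- From the protocol: n = 1,271 per arm (section 1.9) and Fisher's exact test (12.3.3), taken here at the two-sided 5% level.
- Assumed, because the protocol gives no values: p = 10%, 30% or 60%, with q = 50% in the conventional arm and 50%, 55% or 60% in the intensive arm.
- Example: p = 30% with q = 60% v 50% gives 0.30 × 0.60 = 18% v 0.30 × 0.50 = 15%.

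Share of 2,000 simulated trials per scenario in which Fisher's test rejects although the true rates are equal:

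| q, intensive v conventional | p = 10% | p = 30% | p = 60% |
|---|---|---|---|
| 50% v 50% | 4% (5% v 5% reported) | 4% (15% v 15%) | 4% (30% v 30%) |
| 55% v 50% | 8% (5.5% v 5%) | 16% (16.5% v 15%) | 35% (33% v 30%) |
| 60% v 50% | 20% (6% v 5%) | 52% (18% v 15%) | 89% (36% v 30%) |

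The choice of rule also changes the level. Under 11.1 both arms would report 10%, 30% or 60%. Under 11.2 with q = 50% they would report half of that.

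**3. Route through testing frequency (literal 11.1)**

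If each test occasion has chance r of an untoward finding and a subject has k occasions, treated as independent, the chance of at least one is 1 − (1 − r)^k, which rises with k.

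- Section 9.3 places hematology, hepatic and renal tests, electrolytes and CPK at regular hospital visits. Table 2, note 3, ties these to the visits planned for each subject.
- Section 8.2.1, Note 1, sets visits at least once a month until March 2010 for the intensive arm. After that, frequency depends on insulin use and stability.
- Section 8.2.2 states no visit frequency for the conventional arm.

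Equal k is therefore not secured. The size of any difference cannot be calculated, because one of the two frequencies is not stated.

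**4. What lies outside the problem**

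- Hypoglycemia, edema, palpitation and shortness of breath are asked about by checklist in all subjects (11.2, Procedure 2).
- Serious reactions have their own criteria (11.4.1).
- The primary endpoint is defined without these findings (10.1).

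**The case against.** The strongest reply is that 11.1 is terminology and 11.2 is procedure. *Untoward* already calls for judgement, and Procedure 3 merely says who exercises it. This is a fair reading, and it means that 11.1 need not be taken to count every out-of-range value. It does not remove the concern: on this reading, the tested percentage still rests on unblinded judgement without a threshold.

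A reader might go further and infer that under 11.1 nearly everyone becomes a case. With 15 listed analytes, each abnormal in 5%, 10% or 20% of subjects, 1 − (1 − p)^15 gives 54%, 79% or 96%. The protocol does not support this. The calculation treats every out-of-range value as untoward, takes correlated analytes (for example RBC, Hb and Hct, or AST and ALT) as independent, and assumes a single any-reaction percentage, to which 12.3.3 is not restricted. With 8 effective items at 5%, also an assumption, the figure is 1 − 0.95^8 = 34%. Tested reaction by reaction, nothing need saturate.

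It is also fair to say that assumed flagging rates show only what differential ascertainment could do, not that it occurs. The table above has no more force than that.

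There are partial safeguards. Section 11.5 requires a check that no adverse reactions were missed, and Table 2, note 9, gives numerical potassium triggers for re-examination. The first needs a settled definition of what is reportable, and the second is not an adverse-reaction definition.

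Finally, cut-offs by analyte are often left to the statistical analysis plan, so their absence from the protocol is not itself the fault. The fault is that the protocol's own definition and collection rule disagree. A later analysis plan cannot recover adverse reactions that sites never recorded as such. It can use the scheduled laboratory values, which is the basis of the fix.

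**Conclusion.** The point holds for the laboratory component of the adverse-reaction comparison in 12.3.3. Sections 11.1 and 11.2 are not reconciled, and under either one the ascertainment of laboratory reactions can differ by arm: through open-label judgement under 11.2, through unequal testing under a literal 11.1.

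No numerical size can be claimed. The rejection rates of about 8% to 89% rest on assumed abnormality and flagging rates. With equal flagging the test rejects in about 4% of trials, as it should. It would be wrong to infer that the comparison is known to be biased, that the conventional arm is known to be tested less often, or that the percentages carry no information on treatment differences; the protocol shows none of these.

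This is a modest matter of safety reporting. The four checklist symptoms, serious reactions, the primary endpoint and its error rate are untouched. It is worth correcting because the remedy is cheap and uses data already planned.

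**What to change.** 1. Reconcile 11.1 and 11.2, Procedure 3, to one rule for when a laboratory finding is reported as an adverse reaction, worded identically in both places and applied in both arms. The rule should not depend on whether the finding led to an action. In an open-label trial with stepwise titration in one arm, acting on a value is at least as arm-dependent as judging it meaningful.
2. In 12.3.3, base the between-arm laboratory safety comparison on recorded values from the 6- and 12-month examinations (9.4 and 9.5), which are scheduled alike for both arms. Analyse by analyte, with the same cut-offs for both arms fixed before anyone choosing them has seen results by arm.
3. Report these derived rates separately from physician-reported adverse reactions, and give the number tested in each arm at each examination. The last item is needed because section 7.3 continues only serum creatinine and urinary albumin and creatinine, among laboratory tests, in subjects followed after stopping treatment.

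The cost is wording in three sections and some programming, with no new measurements. The downside is that abnormal values seen only at other visits do not enter the derived rates, though they remain reportable as adverse reactions.
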